# CRYSTALLBrain: crystalloid fluid choice and neurological outcome in patients with non-traumatic subarachnoid haemorrhage—a study protocol for a multi-centre randomised double-blind clinical trial

**DOI:** 10.1186/s13063-025-09099-9

**Published:** 2025-10-17

**Keywords:** Subarachnoid haemorrhage, Crystalloid fluid choice, Vasospasms, Outcome, Neurological sequelae

## Abstract

**Background:**

Vasospasms are common in patients presenting with non-traumatic subarachnoid haemorrhage (SAH) and are the main contributor to long-term disability or death in these patients. The key immediate management of vasospasms is the improvement of brain perfusion by the administration of intravenous fluid and vasopressors if needed. Yet, there is no clear recommendation regarding the choice of fluid in this particular patient population. Data suggests a survival benefit using normal saline in patients with TBI; however, its impact on outcomes in patients with SAH is lacking. Thus, the aim of this study is to evaluate whether the use of normal saline reduces clinically relevant vasospasms compared to Ringer’s lactate in patients with SAH.

**Methods:**

Patients presenting with non-traumatic SAH will be randomised 1:1 to normal saline or Ringer’s lactate group. Blinded study fluid will be used exclusively for resuscitation and maintenance until ICU/IMC discharge or a maximum of 14 days, whichever occurs first. Management of vasospasms and general management of the SAH patient will be according to the clinic standard of care. Primary endpoint is the occurrence of clinically relevant vasospasms. Key secondary outcomes include mortality, severity and treatment of vasospasms, and neurological outcomes at 90 days.

**Discussion:**

The proposed randomised controlled trial offers a safe, non-invasive way to gain insights about crystalloid fluid choice in SAH patients, with potential to improve outcomes in this critically ill patient group. This study could establish a new gold standard in fluid therapy for neuro-critical care.

**Trial registration:**

The trial is registered on ClinicalTrials.gov (date of registration 18 June 2021) and on the Swiss National Clinical Trials Portal, SNCTP000004575.

**Supplementary Information:**

The online version contains supplementary material available at 10.1186/s13063-025-09099-9.

## Administrative information

Note: the numbers in curly brackets in this protocol refer to SPIRIT checklist item numbers. The order of the items has been modified to group similar items (see http://www.equator-network.org/reporting-guidelines/spirit-2013-statement-defining-standard-protocol-items-for-clinical-trials/
).

## Introduction

### Background and rationale {6a}

Non-traumatic subarachnoid haemorrhage (SAH) is a devastating disease with a high mortality of up to 50% [1]. More than 50% of the survivors develop cognitive dysfunctions in the long term and never return to their previous status [1]. Most of these patients are Younger than 55, so the disease has a major socio-economic impact in addition to the individual tragedy [1, 2].

Despite the advances in diagnosis and treatment of SAH, effective therapeutic interventions are still limited and clinical outcomes remain disappointing [1]. In addition to the early brain injury caused by the haemorrhage and inflammatory response to it, about one third of the patients with SAH develop delayed cerebral ischaemia (DCI) [3]. DCI is a primary contributor to persistent neurological impairment in patients with SAH [4–6]. DCI often results from vasospasms of proximal cerebral arteries and the microcirculation; however, there might be also other factors contributing to impaired cerebral perfusion and subsequently ischaemic injury, such as seizures, impaired autoregulation with reduction of regional blood flow, microthrombosis, spreading depolarisations, or high intracranial pressures [7]. Yet, approximately half of the patients with angiographic vasospasms progress to develop DCI, and spasms in small vessels may not be detected through standard angiography [5]. The pathophysiology underlying vasospasms, a primary driver of secondary brain injuries, remains incompletely understood; however, evidence suggests that oxidative stress, inflammation in response to haemorrhage, decrease of NO as well as episodes of hyponatraemia contribute to alterations in cerebral arterial diameter [8]. The latter is a common phenomenon in patients with SAH and occurs in 30 to 50% of the patients [9]. Although the only guideline-recommended strategies for reducing DCI include enteral nimodipine administration and the prevention of hypovolaemia and hypotension, primarily through fluid administration, there are currently no specific recommendations regarding the choice of crystalloid fluids for this patient population [10, 11]. Of note, patients with SAH often require several litres of intravenous fluid per day in order to counterbalance overt fluid losses and maintain adequate blood pressure. In a recent meta-analysis, Zampieri and colleagues summarise the current evidence on balanced versus normal saline infusion in critical care [12]. The study indicates a potential survival benefit associated with the use of balanced fluids in the general critical care population [12]. However, the meta-analysis also reveals that the administration of balanced fluids in patients with traumatic brain injury is associated with increased mortality [12]. This finding is consistent with other research suggesting that neuro-intensive care patients may benefit from a higher sodium load [3, 8, 11–13]. Similar might be true for patients with non-traumatic SAH. However, according to the guidelines by the ESICM, no prospective randomised trial has ever evaluated whether the type of infusion fluid used in patients with SAH might influence the incidence of vasospasms, and mortality and morbidity in these patients, and further investigations are highly warranted [11].

### Objectives {7}

#### Hypothesis

We hypothesise that the use of a sodium-enriched solution (0.9% saline) for fluid therapy in patients with non-traumatic SAH will result in a lesser occurrence of clinically significant vasospasm requiring immediate intervention than after treatment with a balanced, formally hypotonic infusion solution (Ringer’s lactate).

#### Primary objective

The primary aim of this study is to evaluate whether the use of normal saline results in lower occurrence of clinically relevant vasospasms when compared to lactated Ringer’s in patients with non-traumatic SAH.

### Trial design {8}

The CrystallBrain study is an investigator-initiated randomised controlled multi-centre double-blind trial comparing 0.9% saline to lactated Ringer’s (two already established treatment protocols) in patients with non-traumatic SAH. Patients will be allocated a 1:1 ratio to either normal saline (0.9%) or lactated Ringer’s.

## Methods: participants, interventions, and outcomes

### Study setting {9}

The study will be carried out in accordance with the protocol and with principles enunciated in the current version of the Declaration of Helsinki, the guidelines of Good Clinical Practice (GCP) issued by ICH [13, 14]. We plan to enrol 320 patients (1:1 randomisation) at Intensive Care Units at the University Hospital Bern, Inselspital, Bern, at the University Hospital Geneva, HUG, Geneva, and at the Canton Hospital St. Gallen.

### Eligibility criteria {10}

#### Inclusion criteria

All adult patients suffering from non-traumatic SAH and admitted to the Intensive Care Unit (ICU) or Intermediate Care Unit of one of the study centres are eligible for inclusion.

#### Exclusion criteria

Patient with major intracranial traumaDiagnosis of an AV-malformation as the source of SAH on the primary CT/MRI or angiography if performed prior to randomisation > 24 h since first diagnosis of SAH (as diagnosed by cerebral imaging [CT or MRI])Patients with clear limitation to therapy at hospital admission (e.g. ICU admission for evaluation of organ donation)

### Who will take informed consent? {26a}

The process leading to informed consent will be in compliance with applicable regulations and national laws. The informed consent procedure will be as follows: independent physician signature will be sought prior to enrolment of the patient. If the patient presents with Glasgow Coma Scale (GCS) 15, then patient consent will be reached prior to randomisation. If the patient is cognitively impaired (GCS < 15), consent of the patient’s next of kin will be sought, with deferred informed consent by the patient. The investigators will explain to each participant or next of kin the nature of the study, its purpose, the procedures involved, the expected duration, the potential risks and benefits, and any discomfort it may entail.

### Additional consent provisions for collection and use of participant data and biological specimens {26b}

No additional biological specimens will be collected and stored. Informed consent for the potential future use of trial data has been obtained from all participants and is documented in the consent form.

## Interventions

### Explanation for the choice of comparators {6b}

Worldwide, 0.9% sodium chloride (normal saline) is the most commonly administered fluid in critical care [15–18]. In contrast to other infusion solutions like lactated Ringer’s, normal saline does not contain other electrolytes than sodium and chloride and is therefore considered a non-buffered solution. Due to the high chloride content, there were rising concerns about the development of metabolic acidosis, kidney injury, and even higher mortality in patients receiving normal saline [17–22]. This in turn has led to the increased use of buffered solutions, such as Ringer’s lactate.

In contrast to isotonic saline, it contains calcium, potassium, magnesium, and the metabolisable anion lactate. Lactate is metabolised to bicarbonate (also referred to as “buffer concept”). This is important for two reasons: First, through infusion of lactate containing solutes, the bicarbonate concentration of the plasma remains stable and is not diluted [23, 24]. Secondly, the use of a metabolisable anion such as lactate saves the use of other anions such as chloride and avoids hyperchloraemia. Studies showed that in comparison to isotonic saline, the occurrence of metabolic acidosis and electrolyte abnormalities is significantly reduced when a balanced infusate is used [25–36]. A recent meta-analysis has revealed that the use of buffered infusion solutions in the critically ill leads to a survival benefit, with the exception of patients with traumatic brain injury, where buffered solutions with lower salt content were associated with higher mortality [12]. However, the impact of fluid choice in patients with non-traumatic SAH is not known. To date, both infusates are used as standard solutions in the treatment of patients with SAH in ICU worldwide.

### Intervention description {11a}

All patients that meet the eligibility criteria as defined above will be randomised 1:1 to either the normal saline group or the Ringer’s lactate group. We will use 0.9% saline and Ringer’s lactate (Bichsel©, Interlaken, Switzerland). Study fluids will be used exclusively for resuscitation and maintenance until ICU/IMC discharge or a maximum of 14 days, whichever occurs first.

Fluid will generally be administered according to haemodynamic and clinical endpoints following standard of care of the participating centres. Patients will receive the allocated study fluid for all fluid therapy during the study period. All other fluid types including colloids will not be administered during the study time with the exception of creep fluid necessary to administer medication. In addition, hypertonic saline perfusion is allowed to treat low sodium levels and for treatment of brain oedema. Mannitol is allowed for the treatment of acute elevation of intracranial pressures and/or brain oedema. During interventions or surgery, continuous treatment with the allocated study fluid will be attempted.

#### Management of vasospasm

All patients with SAH will receive prophylactic treatment with nimodipine if blood pressure allows. Vasospasms are either diagnosed clinically according to the CONCIOUS criteria [6] or radiologically by cerebral Doppler examination, cerebral CT-angiography, and/or CT perfusion imaging. If vasospasms are clinically significant, immediate treatment entails. The augmentation of the mean arterial pressure as the first step of management. The target is set according to the patient’s clinical presentation and is at the discretion of the treating team (intensivist, neurosurgeon). Fluid administration with the allocated fluid type will be the first-line therapy to augment blood pressure, followed by a norepinephrine infusion. If the vasospasms are unresponsive to conventional therapy, the patient will undergo endovascular treatment. The choice of treatment (intra-arterial application of vasodilators or angioplasty) is at the decision of the treating neurosurgeon, interventional neuroradiologist, and/or intensivist.

#### Management of electrolyte disorders

In the case of the occurrence of hypo- or hypernatraemia, concomitant measurement of serum and urine osmolality and urine sodium will be performed to evaluate the nature of the sodium disorder (e.g. diabetes insipidus, syndrome of inappropriate antidiuretic hormone secretion) and treatment will be according to the diagnosis and the clinical situation of the patient following the clinics SOPs. Study fluids will be continued as allocated.

### Criteria for discontinuing or modifying allocated interventions {11b}

The clinical team may at any time violate the protocol if they find it to be in the best interest of the participant. The procedure of handling withdrawal of consent from a participant will follow national regulations. Patients diagnosed with an AV-malformation (AVM) as the source of the non-traumatic SAH after the randomisation (i.e. the AVM was not evident in the initial CT or MRI done prior to randomisation) will drop out of the study and the data will be anonymised for a drop-out analysis.

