### Participant timeline {13}

All eligible patients will be randomised within 24 h of diagnosis (time stamp on first computed tomography or MRI). From randomisation up to discharge from ICU/IMC or day 14 after randomisation, whichever comes first, the patient will receive the allocated study fluids only. Fluid, water, and electrolyte balance will be assessed daily. Serum osmolality and urinary sampling will be performed at hospital admission (day 1) and on days 3, 7, 10, at day 14, or at the day of ICU/IMC discharge, whichever comes first. In addition, blood gas analysis including electrolytes will be performed at a minimum of once a day as long as the patient is in ICU/IMC. In addition, an electrocardiogram and, at the lead centre (University Hospital Bern, Inselspital), bioimpedance measures will be performed on predefined study days (see Table 2 [SPIRIT figure]).

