**Table 2 Tab2:**
[figure not shown]
SPIRIT figure

Neurological outcome will be assessed by the modified Rankin Scale (mRS), Glasgow Outcome Scale Extended (GOSE), and Montreal Cognitive Assessment (miniMOCA) at day 90 (see Supplementary Figures S1–S3). Mortality will be assessed at day 30 and 90.

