## Data collection and management

### Plans for assessment and collection of outcomes {18a} and plans to promote participant retention and complete follow-up {18b}, and data management {19}

Data will be obtained from the participant’s hospital files, study-specific examinations (e.g. bioimpedance results), the Insel Data Science Centre (IDSC) and national registries (mortality data) and by participant survey/interview and entered in the web-based eCRF (REDCap) by authorised trial personnel. For participants transferred from a trial ICU to a non-trial ICU, data related to the outcomes will be collected according to investigator contact with the non-trial ICU.

Long-term disability will be assessed by telephone interview or at the outpatient clinic appointment in the neurosurgical unit based on the modified the mRS, GOSE, and miniMOCA (see Figures S1–S3 in the Supplemental File for more details).

All data will be verified by regular monitoring, as well as data validity checks and automated consistency queries in the trial database. A final data quality check will be performed before the database is closed. All data changes and checks are tracked in the database.

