## Statistical methods

### Statistical methods for primary and secondary outcomes {20a}

This is a parallel group study. All randomised patients receiving the study fluid will be included in the primary analysis according to a modified intention-to-treat (mITT) principle [38]. The analysis is defined as modified because patients in whom an AV-malformation is subsequently identified as the source of the haemorrhage will be excluded, since this underlying condition falls outside the intended study population; their data will contribute only to a drop-out analysis. Normal distribution of continuous variables will be tested with the Shapiro–Wilk test. Normally distributed variables are presented with mean and standard deviation. Skewed or interval and ordinal variables are presented as medians with interquartile ranges. Normally distributed interval and ordinal variables will be compared by unpaired *t*-test and skewed variables by the Wilcoxon rank sum test. Comparisons of categorical variables were performed using chi-square test or Fisher’s exact test, as appropriate [39].

Whether the use of normal saline significantly influences our primary endpoint will be assessed by a logistic regression analysis adjusted for the stratification variables (trial site) in the ITT population [40]. For the primary endpoint, deceased patients or patients who were transferred prior to reaching the primary endpoint will be counted as “no event”. A sensitivity analysis with a modified primary endpoint will be used, defined as a composite endpoint of (i) clinically relevant vasospasms during the first 14 days, (ii) ICU/IMC readmission during the 14 days (if discharged earlier) because of vasospasms, or (iii) death within 14 days.

Our secondary endpoints will be assessed by logistic (binary endpoints) as well as linear regression models (such as mRS, GOSE, and miniMOCA) adjusted for the stratification variable (trial site).

We will report absolute risk difference and relative risk ratios with 95% CIs for dichotomous secondary outcomes. For continuous secondary outcomes, we will report mean differences with 95% CIs. Missing values will be imputed with the use of the last-observation-carried-forward method for measurements made after baseline. *P* values smaller than 0.05 are considered statistically significant. Secondary outcomes will be analysed in an explorative way.

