### Adverse event reporting and harms {22}

Severe adverse events (SAEs) will be reported in a standardised fashion according to Swiss law.

All SAEs are documented and reported immediately (within a maximum of 24 h) to the sponsor-investigator of the study.

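### Patients whose AV-malformation is found after randomisation leave the study with anonymised data although they received study fluid; as written, their later SAEs and deaths are not followed and the by-arm mortality results omit them.

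*Protocol article*

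**What the plan says.** The protocol article, under Criteria for discontinuing or modifying allocated interventions {11b}, covers a patient in whom "the AVM was not evident in the initial CT or MRI done prior to randomisation" and in whom an AVM is later identified as the bleeding source. Such a patient "will drop out of the study and the data will be anonymised for a drop-out analysis". Withdrawal of consent is dealt with separately in the same paragraph, by reference to national regulations.

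Statistical methods for primary and secondary outcomes {20a} defines the analysis set: "All randomised patients receiving the study fluid will be included in the primary analysis according to a modified intention-to-treat (mITT) principle". It then takes the AVM patients out of that set and adds that "their data will contribute only to a drop-out analysis".

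Three other places bear on safety:

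- Adverse event reporting and harms {22}: "All SAEs are documented and reported immediately (within a maximum of 24 h) to the sponsor-investigator of the study".
- Participant timeline {13}, below Table 2: "Mortality will be assessed at day 30 and 90".
- The data collection section {18a, 18b, 19} lists hospital files, participant interviews and "national registries (mortality data") as sources.

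ICU, in-hospital and 90-day mortality are secondary endpoints under Outcomes {12}. There is no data monitoring board {21a} and no interim analysis {21b}.

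**The concern.** Two decisions are joined in one rule. The first is whether a patient with an AVM belongs in the efficacy comparison. The second is whether a patient who was given a blinded study fluid should still be followed for harm. The reason given in {20a}, that AVM lies outside the intended population, answers only the first.

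Exposure does not depend on the bleeding source. The article's own reasons for worrying about the fluids are acidosis, kidney injury and mortality with saline (Explanation for the choice of comparators {6b}) and fluid accumulation (Discussion). None of these is described as limited to aneurysmal or other non-AVM haemorrhage.

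At stake is a safety and mortality comparison that omits some treated patients, in a trial where SAE reporting is the main safety mechanism described. The omission may also be irreversible: an analysis set can be redefined later, but a broken identity link cannot be restored.

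**Working it through.** No figure in the plan is at issue, so the check is mainly a reading of the sections side by side.

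1. **Are these patients exposed?** Yes. {13} says that from randomisation "the patient will receive the allocated study fluids only". {20a} takes the AVM cases out of a set defined by having received study fluid. Late recognition is foreseen: the exclusion criteria rely on the primary CT or MRI, and on angiography only where it was done before randomisation.

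2. **Are SAEs before drop-out covered?** Yes. {22} makes no exception for them, and an anonymised record can still carry arm and events to date.

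3. **Are SAEs after drop-out covered?** Not as written. {11b} takes the patient out of the study, and no section says that SAE reporting continues for someone who has left.

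4. **Are day-30 and day-90 deaths covered?** Not as written. Each listed source (files, interview, registry) needs an identifiable patient. Once the data are anonymised, none of them can be matched to the record.

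5. **Are deaths already recorded counted by arm?** Not in the mortality endpoints, because {20a} allows these data only in the drop-out analysis. That section also names an ITT population for the primary regression, but nothing there returns AVM patients to the mortality results.

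**Scale.** The documents give planned enrolment (320) but no AVM rate, so the rate *a* is an assumption. Number affected = 320 × *a*. Deaths among them = 320 × *a* × *m*, where *m* is either an assumed 20% or the upper figure of 50% quoted for SAH in general under Background and rationale {6a}.

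| Assumed *a* | Patients (both arms) | Deaths at *m* = 20% | Deaths at *m* = 50% |
|---|---|---|---|
| 1% | 3.2 | 0.6 | 1.6 |
| 2% | 6.4 | 1.3 | 3.2 |
| 5% | 16.0 | 3.2 | 8.0 |
| 10% | 32.0 | 6.4 | 16.0 |

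If the whole planned 15% drop-out were AVM, the number would be 320 × 0.15 = 48. The death columns count all deaths in both arms, including any before drop-out. They bound what the mortality results could omit and do not estimate what would be lost to follow-up.

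**The case against.** The strongest reply is that the text does not say when anonymisation takes place. It could be at diagnosis, at study end, or only when a dataset is extracted for the drop-out analysis. If it comes after day 90, linkage might survive. SAE reporting is worded without exceptions, and the length of follow-up after discontinuation and the definition of a safety set are details that an article may leave to the full protocol or SAP.

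Part of this stands. A reader might infer that events in these patients cannot be counted by arm at all. The documents do not support that: SAEs before drop-out are reportable, and the arm label may remain. The timing of anonymisation is also open.

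The rest does not remove the point. The article states a rule here: leave the study, anonymise, use only in a drop-out analysis. A safety set defined later in a SAP could not recover follow-up that was never collected. If late anonymisation with continued follow-up is intended, {11b} says something different and needs correcting.

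A second tempting inference is that removal favours one arm, because a patient must survive to further imaging for an AVM to be found. That concerns membership of the mITT efficacy set, which this point leaves unchanged. AVM is a baseline condition, and care providers and outcome assessors are blinded. Nothing in the documents shows that the fluid alters survival to imaging or the imaging itself, so bias between arms is not established.

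It is also fair to say that both fluids are established and that the trial was categorised as low risk. That limits the weight of the point without justifying the loss of follow-up.

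**Conclusion.** The point holds in a limited form. As written, patients who received study fluid and are later found to have an AVM are not followed for SAEs or death after drop-out, and the by-arm mortality results leave them out. Once their data are anonymised, that follow-up can no longer be obtained.

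The number is unknown and probably small: about 6–16 of 320 if 2–5% are affected, which is an assumption. No number of lost deaths should be read from this. The 50% mortality is an upper figure for SAH in general, and some deaths would precede drop-out. The primary efficacy analysis is untouched. The conclusion rests on taking leaving the study to mean the end of follow-up, which is the plain reading and is contradicted nowhere in the article. It deserves an amendment because the loss is avoidable and cheap to prevent.

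**What to change.** Keep the exclusion of AVM patients from the mITT efficacy analysis. Leave any decision on study fluid to the existing text and the treating team; the change below concerns data and follow-up only.

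- **{11b}:** separate leaving the efficacy analysis from ending follow-up. State that data stay coded as for all other patients, that SAE follow-up and vital status to day 90 continue unless consent is withdrawn, and that any anonymisation happens only after that.
- **{20a}:** replace the restriction to a drop-out analysis with a safety set of all randomised patients who received any study fluid, AVM patients included. Report SAEs and ICU, in-hospital and 90-day mortality by arm in that set.

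The cost is a small amount of extra follow-up through sources already in use, one additional table, and an ethics-approved amendment with a check that the consent form covers continued follow-up. At the Trial status statement, 157 of 320 patients had been randomised, leaving 320 − 157 = 163 to come. Records already anonymised may not be recoverable. Their number should be reported, by arm if the label was kept, so that readers can see how complete the safety set is.
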